## Abstract

**Introduction:**

Nearly half of patients who receive invasive mechanical ventilation for acute respiratory failure require over 4 days of ventilator support, each day of which is associated with increased morbidity, mortality and cost. Many of these patients develop expiratory muscle atrophy and weakness, which are linked to failed extubation and weaning. We seek to test the hypothesis that exhalation synchronised abdominal functional electrical stimulation reduces mechanical ventilation duration.

**Methods and analysis:**

This pivotal superiority trial will be performed in up to 30 intensive care units (ICUs) in the USA, France, the Netherlands and Australia. Adults (≥22 years old) who have been mechanically ventilated for 24–96 hours and are expected to remain ventilated for another 24+ hours are potentially eligible. We will recruit participants until 150 successful liberations from mechanical ventilation occur. To achieve this, we estimate that a maximum of 272 participants will be randomised in a 1:1 ratio to receive 30 min of active exhalation synchronised abdominal functional electrical stimulation (vs sham). The intervention will be applied using the VentFree Respiratory Muscle Stimulator two times per day, a minimum of 5 days per week, for a maximum of 28 days or until ICU discharge. The primary outcome is time from first intervention to successful liberation from mechanical ventilation. Secondary outcomes include cough peak flow (CPF) and maximum expiratory pressure (MEP) at 24 hours post-extubation, hospital and ICU length of stay, reintubations, complications, ICU readmissions, 90-day mortality and quality of life. The participant, clinical team and outcome assessor are blinded to group allocation. A positive outcome has the potential to improve patient-centred outcomes in ICUs.

**Ethics and dissemination:**

This study was approved by local ethics institutions in the USA, Australia, France and the Netherlands. We describe the methods herein using the Standard Protocol Items for Randomised Trials framework and discuss key design decisions. The results will be disseminated through peer-reviewed journal publications, conference presentations and clinicaltrials.gov updates. Individual country-level approvals are as follows:

France:

Australia:

Netherlands:

USA:

All participating sites are currently approved and operating under protocol version 09 or later.

**Trial registration number:**

NCT05759013. Registered 8 March 2023.

STRENGTHS AND LIMITATIONS OF THIS STUDYThe standard weaning protocol developed for this trial will improve consistency across the 30 study sites.The screening method for awakening and comprehension will improve the quality of pulmonary function data collected in the trial.The international design of the trial, which includes three continents, will improve generalisability of the trial results.The optimum stimulation parameters for abdominal functional electrical stimulation have yet to be established and, as such, the treatment protocol has been chosen based on physiological and practical considerations.

## Introduction

 Mechanical ventilation is a life-saving intervention for patients with acute respiratory failure,^1^ but this invasive medical therapy has been linked to adverse and often life-threatening complications including ventilator-induced lung injury, muscle weakness and delirium.^2^,^5^ The probability of survival decreases as duration of ventilator support increases^1^ with prolonged intensive care unit (ICU) stays associated with functional disability and increased mortality up to 1 year post discharge.^3^ Accordingly, treatments that reduce duration of mechanical ventilation may also reduce morbidity and mortality, improve quality of life and reduce healthcare costs.

The respiratory muscles play an important role in liberation from mechanical ventilation,^6^,^11^ with expiratory muscle strength an independent predictor of liberation success^12^,^16^ and delayed extubation.^13^ In addition, an effective cough predicts liberation success, morbidity and mortality.^17^,^19^ However, ~40% of mechanically ventilated patients lose >10% of diaphragm mass^8^ and 30% experience a loss of abdominal muscle mass^10^ during the first 5 days of mechanical ventilation. This results in a large reduction in force generation,^5 7 8^ with these patients experiencing considerable expiratory muscle weakness and a reduction in respiratory function.^10 19 20^ Therefore, improvements in expiratory muscle strength have the potential to reduce duration of mechanical ventilation and increase the likelihood of successful ventilator liberation.

Inspiratory muscle training using a threshold loading device^21^ and temporary transvenous phrenic nerve stimulation^22^ are two therapies that target respiratory muscle atrophy during mechanically ventilated patients. While the benefit of inspiratory muscle training for critically ill patients remains uncertain,^23 24^ this therapy depends on patient motivation and cooperation, which can limit its effectiveness during critical illness. Temporary transvenous phrenic nerve stimulation has been shown to improve maximal inspiratory pressure, but this finding has not yet translated to an increased proportion of patients being liberated from mechanical ventilation.^22^ Furthermore, this invasive technique requires a central venous catheter fitted with pacing electrodes.

Neuromuscular electrical stimulation, the application of small electrical pulses to the motor nerves supplying a muscle to elicit a contraction, has been shown to be a safe and effective technique to reduce muscle atrophy and critical illness polyneuromyopathy in critically ill patients.^25^ When neuromuscular electrical stimulation is applied to the abdominal wall muscles in synchrony with exhalation, termed abdominal functional electrical stimulation, the effect on ventilation is similar to a physiological contraction of the abdominal wall muscles. Previous studies have shown that abdominal functional electrical stimulation can acutely improve respiratory function^26^ and increase tidal volume and reduce duration of mechanical ventilation for people with tetraplegia.^27^ Importantly, abdominal functional electrical stimulation does not require patient cooperation.

We completed two pilot clinical trials that examined abdominal functional electrical stimulation using the VentFree device during invasive mechanical ventilation in critically ill patients.^28 29^ Both studies demonstrated the feasibility of applying this technology with critically ill mechanically ventilated patients. Notably, median ventilation duration and ICU length of stay were 10 versus 52 days (p=0.07) and 12 versus 54 days (p=0.03) for the intervention versus sham group, respectively. No serious device-related adverse events occurred, and treatment session compliance was >90%.^30^

The primary objective of the Pivotal Evaluation of Abdominal Functional Electrical Stimulation using the VentFree device for Weaning from Mechanical Ventilation (PREVENT) trial is to determine whether using the VentFree device reduces the time from first treatment to successful liberation from mechanical ventilation in critically ill adult patients.

## Methods

### Trial design

PREVENT is a randomised, sham-controlled, participant and assessor-blinded, multicentre clinical trial. It uses a superiority design to compare active and sham abdominal functional electrical stimulation on mechanical ventilation duration.

### Study setting

Participants will be enrolled in up to 30 sites in the USA, France, the Netherlands and Australia. No more than 25% (68 participants) of the study population will be enrolled at any single site and no more than 45% of participants outside the USA. A full list of all participating sites can be found at https://clinicaltrials.gov/study/NCT05759013.

### Eligibility criteria

#### Inclusion criteria

Participants must meet both of the following inclusion criteria:

≥22 years of age (as per American medical device regulations).Invasively mechanically ventilated ≥24 hours.

#### Exclusion criteria

Participants must meet none of the following exclusion criteria:

Invasively mechanically ventilated for >96 hours prior to randomisation.Expected to be disconnected from mechanical ventilation ≤24 hours after enrolment.Intubated for ≥24 hours during a prior episode of invasive mechanical ventilation during the current hospitalisation.Body mass index (BMI) ≥40 kg/m^2^.No contraction of abdominal wall muscles in response to abdominal functional electrical stimulation (determined by ultrasound).Pre-existing neuromuscular or muscular disorder that could affect the respiratory muscles (eg, spinal cord injury or Guillain-Barré syndrome).Open abdominal surgery <4 weeks prior to enrolment.Open or damaged skin at the area of electrode placements.Pacemaker and/or implanted electronic device.Known or expected pregnancy.Pharmacological paralysis at the time of enrolment (those receiving neuromuscular blockers may be enrolled after a ≥12-hour washout period).Tracheostomy prior to enrolment.On home non-invasive ventilation (except for Continuous Positive Airway Pressure (CPAP) or Bilevel Positive Airway Pressure(BiPAP) for obstructive sleep apnoea).Receiving or expected to receive comfort measures (palliative, hospice, comfort care, etc.) at the time of screening or enrolment.Participation in any of the following:A study with the same or similar primary outcome.A study investigating electrical stimulation or respiratory muscle therapy.Any study which the site principal investigator (PI) determines may interfere with the results of this study.Unable or unwilling to comply with protocol requirements, including assessments, tests and follow-up visits.Any other medical condition which, in the opinion of the investigator, will make participation medically unsafe or will interfere with the study results.Inability to obtain written informed consent from the participant or their legally authorised representative.

### Enrolment and consent

Prior to enrolment, a potential participant, or their legally authorised representative (LAR) for participants who are unable to provide consent due to lack of capacity, will be fully informed of the nature of the trial, details of study procedures, anticipated benefits and potential risks of study participation by the site PI or a suitably trained delegate such as a research co-ordinator. Written informed consent will be provided by the participant/LAR to the site PI or a suitably trained delegate before any study-specific procedures (including screening and baseline tests) are performed. The master participant consent form is provided as online supplemental appendix A. For sites with e-consent capabilities, the signature of the LAR may be obtained electronically. Patients previously incapacitated will be invited to reconsent once they are judged by the site PI to have regained decision-making capacity. No incentives (financial or otherwise) were offered for this trial.

### Eligibility screening

All participants who meet the study inclusion criteria will be pre-screened prior to obtaining informed consent. After a patient’s medical history has been reviewed, informed consent will be obtained from potentially eligible patients before screening is completed. Women of childbearing potential will undergo a pregnancy test. Patients who meet all eligibility criteria will then undergo a test VentFree intervention session to determine if there is contraction of the abdominal wall muscles.

Electrodes will be placed posterior laterally over the abdominal wall designed to activate the transversus abdominis and internal and external oblique muscles (figure 1).^29^

**Figure 1 F1:**
[figure not shown]
Illustration of the VentFree Respiratory Muscle Stimulator setup. The image shows a participant connected to mechanical ventilation with stimulation triggered using a flow sensor connected to ventilator tubing. Alternatively, stimulation can be triggered using a nasal cannula (not shown).

First, the sham group intensity will be determined during this screening abdominal FES session. This will be conducted by administering the abdominal FES at a frequency of 30 Hz, a pulse width of 350 µs and an amplitude of stimulation insufficient to elicit abdominal wall muscle contraction. The initial stimulation amplitude will be set at 10 mA. In the event that ultrasound confirmation indicates muscle contraction at 10 mA, the amplitude will be systematically reduced in increments of 2 mA, with confirmation sought at each step until muscle contraction is no longer observed. This amplitude will serve as the sham stimulation intensity for all sham treatment sessions.

Next, trains of stimulation pulses, 1–2 s in length with incremental intensities (max. 100 mA), will be given to determine the stimulation threshold for tetanic muscle contraction (‘threshold intensity’). To verify contraction, all three layers of the lateral abdominal muscles, namely the internal and external obliques and the transverse abdominis, must be visible on the ultrasound image. A change in the combined thickness of the three muscle layers should be observed in response to stimulation to confirm eligibility for the trial. Stimulation increments will be made based on the participant’s maximum tolerable level. In communicative participants, discomfort associated with the maximum tolerable level will be recorded on a Visual Analogue Scale with pain ratings from 0 (no pain) to 10 (worst pain). In uncommunicative participants, the maximum tolerable level will be determined as the stimulation intensity that results in a Behavioural Pain Scale^31^ score >4 or a Critical-Care Pain Observation Tool^32^ score >2. If stimulation at 100 mA did not result in a visible contraction of the abdominal wall muscles as verified by ultrasound, the patient is ineligible for the trial. Multiple attempts are permissible prior to randomisation as long as the potential participant continues to meet all eligibility criteria. Once eligibility is confirmed, baseline demographic data will be collected.

### Interventions

Participants will be randomly assigned to receive active stimulation delivered using the VentFree device or sham.

VentFree is composed of a control unit, breathing sensors (ventilator circuit flow sensor and nasal-oral cannula), disposable transcutaneous stimulation electrodes and a power supply. The ventilator circuit flow sensor, which is placed between the ventilator tubing and the participant interface (eg, endotracheal tube), is used for all patients who are endotracheally intubated, have a tracheostomy or are receiving non-invasive ventilation. For those liberated from mechanical ventilation, the nasal-oral cannula serves as a flow sensor—which is placed with the nasal prongs inserted in the participant’s nares and the oral prong suspended over their mouth. The nasal-oral cannula can be used together with either a high-flow or conventional oxygen cannula and can be used with most brands of high flow nasal cannula. Using the breathing sensor, the control unit monitors the breathing pattern of the participant to apply functional electrical stimulation in synchrony with exhalation. Figure 1 illustrates VentFree setup when using the ventilator circuit flow sensor. The stimulation electrodes and ventilator circuit flow sensor are replaced every 5 days of treatment and for every treated participant. The nasal-oral cannula is replaced after every treatment session.

All participants will receive 30 min of the VentFree intervention (or sham) twice per day, for a minimum of 5 days per week, for 28 days or until ICU discharge, whichever comes first.

Discharge from the ICU will be defined as the initial occurrence of any of the following:

Transfer order to a general or surgical floor team; orTransfer to a general or surgical floor; orDischarge from the ICU to an outside facility or home.

The first intervention session must be initiated ≤2 hours after randomisation, and a minimum of 4 hours is required between treatment sessions. Training will be provided by the sponsor for all trial procedures.

### Treatment group

In the active treatment group, the VentFree device will be applied with a frequency of 30 Hz and a pulse width of 350 μs. During each stimulation session, the stimulation amplitude will be set to 90% of the participant’s maximum tolerable level, determined using the approach previously described on a daily basis.

While stimulation sessions may occur with participants in the prone position, the optimal positioning for stimulation is supine. If stimulation is to be applied with the patient in the prone position, the patient should be rolled to allow electrodes to be positioned as outlined above. It is important to note that following completion of a prone stimulation session, electrodes must be promptly removed, properly stored and retained for subsequent use, if applicable.

If a participant receives neuromuscular blockade during the trial, all stimulation sessions should continue. In this case, there is no required wash-out period (as required before the initial test VentFree session) between the administration of the neuromuscular blockers and VentFree intervention. However, where practical, the stimulation session after the administration of neuromuscular blockers should be delayed for as long as possible.

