### Strategies to improve adherence to interventions

Stimulation parameters are titrated to avoid participant discomfort at every treatment session. We believe this is an effective way to improve adherence in this trial. Furthermore, after the first week, stimulation is only applied on 5 of 7 days to hopefully improve adherence.

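### Sessions continue under neuromuscular blockade, but the daily amplitude titration then has no usable endpoint below the 100 mA limit

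*Protocol article*

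**What the plan says.** All of the relevant text is in the protocol article.

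- **Treatment group, on blockade:** "If a participant receives neuromuscular blockade during the trial, all stimulation sessions should continue". The section adds that "there is no required wash-out period (as required before the initial test VentFree session", and then that "where practical, the stimulation session after the administration of neuromuscular blockers should be delayed for as long as possible".
- **Treatment group, on amplitude:** in each active session "the stimulation amplitude will be set to 90% of the participant’s maximum tolerable level, determined using the approach previously described on a daily basis".
- **Eligibility screening (text after Figure 1), the approach referred to:** "In uncommunicative participants, the maximum tolerable level will be determined as the stimulation intensity that results in a Behavioural Pain Scale" score above 4, or a CPOT score above 2. The test trains are given "with incremental intensities (max. 100 mA").
- **Exclusion criteria:** pharmacological paralysis at enrolment is an exclusion, although "those receiving neuromuscular blockers may be enrolled after a ≥12-hour washout period".
- **Table 1:** BPS above 4 or CPOT above 2 bars the start of a session but is not in the pause column. That column lists a rise of more than 20 in heart rate or in systolic pressure; limits on heart rate, mean arterial pressure, respiratory rate and oxygen saturation; a seizure; and a request by the participant to stop.
- **Strategies to improve adherence to interventions:** "Stimulation parameters are titrated to avoid participant discomfort at every treatment session".
- **Sham group, with Eligibility screening:** the sham amplitude is found once at screening, starting at 10 mA and reduced if contraction is seen, and is then kept for every sham session.

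**The concern.** Two stated rules do not work together. One continues treatment during blockade. The other sets the amplitude each day by raising the current until the participant shows pain behaviour. A participant under blockade is uncommunicative, so the behavioural endpoint is the one that applies, and it depends on a response that paralysis would be expected to abolish.

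Two safeguards that depend on the participant's response are lost with it. The pain-score bar to starting a session uses the same thresholds, and a paralysed participant cannot ask to stop.

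What is at stake is mainly safety and the description of the treatment given. Some active participants could receive an amplitude that was never checked against discomfort on that day, while the article says that every session is titrated to avoid it. Device-related adverse events are a secondary outcome, so a reader of the results would want to see these sessions apart from the rest.

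**Working it through.** The plan gives no figure of its own for amplitude under blockade, so the check is mainly a comparison of the rules, with one line of arithmetic.

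1. **Do sessions take place under blockade?** Yes. Treatment group says that they should continue. The wash-out that applies before the initial test session is expressly not required later. Delay is requested where practical, but no minimum is set.

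2. **How is the amplitude of those sessions set?** By the general active-arm rule: amplitude = 0.90 x maximum tolerable level, with the level re-determined daily. The article states no exception for blockade. In particular, it does not say that the last level found without blockade is carried forward.

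3. **What ends the daily titration?** For a communicative participant, reported discomfort. For an uncommunicative one, BPS above 4 or CPOT above 2. No third endpoint is given.

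4. **Can that endpoint be reached under blockade?** It relies on observed behaviour, which a paralysed participant would not be expected to show. This step is reasoning, not a statement in the article, and it weakens if blockade is partial or wearing off. The article's own rules before enrolment fit with it: the test session is not done until at least 12 hours after blockers.

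5. **What limit is left?** The 100 mA maximum stated for the test trains, if it carries over with the approach. If titration reached that limit, the session amplitude would be 0.90 x 100 mA = 90 mA.

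6. **Which arm?** Active only. The sham level is fixed at screening at 10 mA or less and is not re-titrated.

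7. **Do the Table 1 criteria fill the gap?**

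| Criterion | Works under paralysis? | Sets the amplitude? |
|---|---|---|
| BPS above 4 or CPOT above 2 (bars starting) | Not expected to | Same scores are the titration endpoint |
| Participant's refusal or request to stop | No | No |
| Heart rate or systolic rise of more than 20 | Yes | No, pauses the session |
| Limits on heart rate, mean arterial pressure, oxygen saturation | Yes | No, pauses or bars the session |

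Some protection therefore remains during a session, but nothing replaces the missing titration endpoint.

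8. **How many sessions?** Number = blocked active participants x blocked treatment days x 2 sessions a day. The article gives neither of the first two terms. Purely as an assumption, take 5% to 20% of 136 active participants (272/2), blocked for 1 to 3 days. That is 7 to 27 participants and 7 x 1 x 2 = 14 to 27 x 3 x 2 = 162 sessions. The range is nearly twelvefold and carries no information beyond its assumptions.

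**The case against.** The strongest reply is that this is a condensed article. The full clinical investigation plan and the sponsor's training are not shown, and bedside detail on titration may well be there. That stands as a caution: the full protocol may settle the point. It does not remove the point, because the article itself states a rule for blockade and a rule for amplitude, and the second has no workable endpoint when the first applies.

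Several stronger readings are tempting, and the text does not support them:

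- *Sessions are compulsory under blockade.* The word used is should, and delay is requested where practical.
- *Pain behaviour is the only restraint.* There is the 100 mA limit, and Table 1's heart rate and pressure criteria need no behaviour from the participant. The representative may also withdraw the participant, and the investigator may stop treatment for safety.
- *The device would run at its maximum.* The 100 mA figure is given for the test trains and is not called the device's limit. Sessions would run at up to 90 mA, a level open to any active participant who tolerates 100 mA. The wide gap from sham is intended.
- *Stimulation under blockade cannot produce a contraction.* The article nowhere says so. The wash-out and ultrasound rules serve eligibility, Treatment group deliberately separates the test session from later sessions, and depth of blockade varies.
- *Exposure is overstated and the comparison is damaged.* No section says how these sessions are counted. The primary analysis is by intention to treat, whatever stimulation was received, and any dilution from ineffective sessions would work against a superiority claim.

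**Conclusion.** The point holds in a limited form. As written, daily titration in an active participant under neuromuscular blockade has no usable endpoint below 100 mA, so up to 90 mA could be delivered without a working check on discomfort. The article's assurance about every session cannot be met for these participants. The vital-sign criteria in Table 1 reduce the risk but do not set the amplitude.

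This rests on three assumptions: that paralysis prevents the scored behaviour, that the 100 mA limit carries over from screening to daily titration, and that the full protocol has no separate provision. The frequency is unknown. The validity of the primary test and the sample size are not in question. The consequence lies in participant safety and in how the treatment is reported, which is enough to justify action at the low cost involved.

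**What to change.** Reconcile Exclusion criteria, Eligibility screening, Treatment group, Table 1 and Strategies to improve adherence to interventions on how the amplitude is determined during neuromuscular blockade. If the full protocol already covers this, the article's wording should reflect it. No dose or clinical rule is proposed here.

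The Trial status section says that recruitment was completed in January 2026, and treatment lasts at most 28 days. New instructions to sites would therefore reach few or no sessions, and the useful step is now in reporting:

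- Identify sessions given under blockade by linking existing treatment and medication records, where these allow it.
- Report the number of such sessions, their amplitude and the device-related adverse events separately in the exposure and safety tables.
- State how the amplitude was in practice determined for them, and qualify the general statement about discomfort.
- If the records do not show blockade status by session, say so.

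The cost is some data linkage and a few extra table rows, with no change to the primary analysis. It is best specified before the analysis, which the article expects to begin in April 2026.
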